## Abstract

**Background:**

Periodontal intrabony defects are usually treated surgically with the aim of increasing attachment and bone levels and reducing risk of progression. However, recent studies have suggested that a minimally invasive non-surgical therapy (MINST) leads to considerable clinical and radiographic defect depth reductions in intrabony defects. The aim of this study is to compare the efficacy of a modified MINST approach with a surgical approach (modified minimally invasive surgical therapy, M-MIST) for the treatment of intrabony defects.

**Methods:**

This is a parallel-group, single-centre, examiner-blind non-inferiority randomised controlled trial with a sample size of 66 patients. Inclusion criteria are age 25–70, diagnosis of periodontitis stage III or IV (grades A to C), presence of ≥ 1 ‘intrabony defect’ with probing pocket depth (PPD) > 5 mm and intrabony defect depth ≥ 3 mm. Smokers and patients who received previous periodontal treatment to the study site within the last 12 months will be excluded. Patients will be randomly assigned to either the modified MINST or the M-MIST protocol and will be assessed up to 15 months following initial therapy. The primary outcome of the study is radiographic intrabony defect depth change at 15 months follow-up. Secondary outcomes are PPD and clinical attachment level change, inflammatory markers and growth factors in gingival crevicular fluid, bacterial detection, gingival inflammation and healing (as measured by geometric thermal camera imaging in a subset of 10 test and 10 control patients) and patient-reported outcomes.

**Discussion:**

This study will produce evidence about the clinical efficacy and potential applicability of a modified MINST protocol for the treatment of periodontal intrabony defects, as a less invasive alternative to the use of surgical procedures.

**Trial registration:**

ClinicalTrials.gov, NCT03797807. Registered on 9 January 2019.

## Background

Periodontal diseases are inflammatory conditions that affect the supporting apparatus of the teeth. Periodontitis and its non-destructive partner condition, gingivitis, are collectively one of the most prevalent inflammatory conditions of humanity [1]. In 2010, severe periodontitis was estimated to be the sixth most prevalent disease in the world, with a prevalence of 11.2%, gradually increasing with age [1]. In periodontitis, the presence of subgingival plaque biofilms in susceptible individuals determines an inflammatory reaction, leading to loss of the supporting connective tissue and alveolar bone. Periodontitis is now classified into different stages (I to IV), based on disease severity, and into grades (A to C), based on risk of progression [2]. Periodontal osseous destruction can result in horizontal or vertical bony defects, depending on the direction and extent of the apical propagation of the plaque-induced lesion [3]. The treatment of periodontitis involves a non-specific reduction of the bacterial load below the gingival margin [4], which can be achieved by oral hygiene instructions and non-surgical periodontal therapy (NSPT). More advanced cases need surgical treatment or extractions. The overall objective of the treatment is the elimination of periodontal inflammation through disruption of the subgingival biofilm, with reduction of gingival probing pocket depth (PPD) and clinical attachment loss (CAL), resulting in reduced risk of disease progression [5–7].

Periodontal vertical bony defects (intrabony defects) have been associated with a higher risk of progression and eventually tooth loss [8]. Therefore, they are considered sites requiring therapy, often beyond NSPT. The treatment of intrabony defects has gradually evolved from radical surgical elimination of the defect by removal of some of the adjacent healthy supportive or non-supportive bone [9] to more conservative surgical approaches [10] and then to regenerative surgical procedures resulting in regeneration of periodontal attachment measurable clinically, radiographically and histologically [11]. However, even these less invasive surgeries are associated with potential morbidity and high costs due to the use of bone graft and barrier materials, and they are not always predictable [12]. More recently, minimally invasive surgical therapy (MIST), modified minimally invasive surgical therapy (M-MIST) and single-flap approach [13] techniques were introduced, adapting regenerative procedures to the principles of minimally invasive surgery. Results of studies using these techniques suggest that the use of biomaterials may not be so crucial for obtaining periodontal regeneration [14]. A recent consensus report of the American Academy of Periodontology considers surgical intervention still the treatment of choice for intrabony defects [15].

Pushing the boundaries of minimal invasiveness, a minimally invasive non-surgical therapy (MINST) protocol has recently been proposed for the treatment of intrabony defects [16]. A recent retrospective analysis has revealed a reduction in bony defect of approximately 3 mm for cases treated with MINST in non-smokers [17]. This improvement seems to be stable at least up to 5 years after treatment, despite no surgical intervention [18]. The effect of MINST may be mediated by improved blood flow and stable blood clot in the intrabony defect. However, no study to our knowledge has tested the efficacy of MINST compared with traditional NSPT followed by surgical intervention (M-MIST) in the osseous healing of intrabony defects.

The primary objective of this study is to compare the efficacy of a further refinement of the MINST approach (modified MINST) with a surgical approach (M-MIST) for the treatment of intrabony defects. Secondary objectives are to (1) compare radiographic intrabony angle change from before to after treatment and between groups; (2) investigate the association between local factors (gingival blood flow, gingival crevicular fluid [GCF] concentration of inflammatory markers, lipids and growth factors, bacterial presence) and intrabony defect depth healing; and (3) investigate the association between patient-based demographic and health-related factors (age, gender, medical history, body mass index [BMI]) and intrabony defect depth healing.

## Methods/design

This is a parallel-group, single-centre, examiner-blind, non-inferiority randomised controlled trial (RCT) to compare the effect of the following interventions in the healing of periodontal intrabony defects in 66 patients with chronic periodontitis (CP):A novel non-surgical treatment protocol (modified MINST)A surgical protocol (M-MIST).

### Inclusion criteria

The following criteria will be required for inclusion in the study:Age 25–70Diagnosis of ‘periodontitis’ stage III or IV (grades A to C)Presence of ≥ 1 ‘intrabony defect’ (PPD, > 5 mm with intrabony defect depth ≥ 3 mm at screening radiograph)Signed informed consent.

### Exclusion criteria

The exclusion criteria are as follows:Smoking (current or in past 5 years)Medical history including diabetes or hepatic or renal disease or other serious medical conditions or transmittable diseasesHistory of conditions requiring prophylactic antibiotic coverage prior to invasive dental proceduresAnti-inflammatory or anticoagulant therapy during the month preceding the baseline examSystemic antibiotic therapy during the 3 months preceding the baseline examHistory of alcohol or drug abuseSelf-reported pregnancy or lactationOther severe acute or chronic medical or psychiatric condition or laboratory abnormality that according to the investigator may increase the risk associated with trial participationPeriodontal treatment to the study site within the last 12 months.

### Study design/plan

All patients will be recruited from the Restorative and Periodontal new patient clinics at Barts and The London Dental Hospital, where potentially suitable new periodontitis patients will be informed about the study. Then a member of the research team will approach potentially interested patients, will provide more information about the study procedures together with the benefits and risks of participation and will give suitable patients the patient information sheet, which they will be advised to read carefully. Potential participants will be informed that they will be allowed to withdraw their participation at any stage of the study. The patients will then be contacted within 1 week to enquire about their willingness to take part in the study and to give them the opportunity to ask any questions about it. Upon agreeing to partake, they will be offered a baseline appointment. Written informed consent (including clinical procedures and collection of study samples) will be obtained before enrolment. Informed consent will follow the Barts and The London Dental Hospital and Queen Mary University of London (QMUL) standard operating procedures and will be conducted by staff trained in taking consent.

### Study visits

Each subject will attend between 8 and 13 study visits over a period of approximately 16 months (see Table 1 for the study visit schedule and procedures). All the visits will take place in the clinics of Barts and The London Dental Hospital. The schedule of assessments is also presented in Fig. 1 (flowchart of study plan and visits) and in Fig. 2 in the form of a Consolidated Standards of Reporting Trials (CONSORT) diagram.

**Table 1 Tab1:** Schedule of study visits and procedures

Protocol procedures	Visit 1	Visit 2	Visit 2a	Visit 2b	Visit 3	Visit 4	Visit 4a	Visit 4b	Visit 4c	Visit 5	Visit 6	Visit 7	Visit 8
	Baseline	Side I treatment	1day post-treatment	5 days post-treatment	Side II treatment	3 months post- treatment	Surgical treatment	1 week suture removal	1 month review	6 months post- treatment	9 months post- treatment	12 months post- treatment	15 months post- treatment
	Week 0		GTI subgroup only	GTI subgroup only			Only subjects in MIST group	Only subjects in MIST group	Only subjects in MIST group				
Verification inclusion/exclusion, informed consent	x												
Medical/dental history & updates Demographics	x	x	x	x	x	x	x	x	x	x	x	x	x
Height, weight, waist circumference	x												
3D facial imaging	x		x	x		x		x	x		x		
Periodontal measurements (PPD, gingival recession, bleeding on probing, mobility and furcation involvement)	x					x				x	x		x
Plaque assessment	x					x				x	x	x	x
PROMs	x		x	x		x		x			x		x
Early healing index	x							x					
Standardised X-ray		x									x		x
GCF collection	x		x	x		x					x		x
Subgingival plaque collection/saliva	x		x	x		x					x		x
Debridement	x					x				x		x	
Impression for radiographic stent	x												
Dentine/root sensitivity measurements	x		x	x		x					x		x

**Fig. 1 Fig1:**
[figure not shown]
Flowchart of study plan and visits

**Fig. 2 Fig2:**
[figure not shown]
CONSORT flowchart

### Study procedures

#### Medical history

A complete medical history will be obtained at the screening visit, including demographic background information and dental status information. This will be reviewed and updated throughout the study. All concomitant medications, procedures and adjunctive product use will be monitored and recorded throughout the study. Tobacco use history will be recorded at baseline based on self-report. BMI will be calculated after measuring the participant’s height and weight.

#### Clinical periodontal assessment

The following periodontal measurements will be taken by the calibrated examiner (author VK) at six sites/tooth using a manual University of North Carolina (UNC-15) periodontal probe (Hu-Friedy, Chicago, IL, USA): dichotomous full-mouth plaque score (FMPS) [19], full-mouth PPD, recession of the gingival margin from the cemento-enamel junction (CEJ), dichotomous 6-point full-mouth bleeding score (FMBS) on probing [19], tooth mobility [20] and furcation involvement with a Nabers probe (Hu-Friedy) [21]. Clinical attachment level (CAL) will be calculated as PPD+ recession. The early healing index [22] will be measured for controls 1 week after surgery. Dentine/root sensitivity (DS/RS) will be assessed on the tested intrabony tooth and on the two neighboring teeth, following isolation using cotton wool rolls, by using an evaporative/thermal stimulus from a 1-s blast of air from a dental unit syringe at 40–65 psi (19–23 °C) directed perpendicular to the tooth surface at a distance of 0.5–1 cm to the exposed root surface (evaporative examination) [23]. Following the air blast, the subject will be given a visual analogue scale (VAS) form to complete each assessment. The VAS is scored from 0 = no pain to 10 = extreme pain, and the subject can indicate the degree of discomfort by indicating either a numerical value from 0 to 10 or by marking vertically across the VAS.

#### Repeatability

Following initial training, for a repeatability exercise the examiner and back-up examiner will perform repeated examinations on 10 subjects for PPD and recession with at least 15 min separation. Upon completion of all measurements, intra-examiner repeatability for PPD measurements will be assessed. In order to test inter-examiner repeatability, at least 10 subjects will be probed twice (once by each examiner). The reproducibility of the examiner will be tested using the Bland–Altman approach [24] and by calculating Lin’s concordance correlation coefficient [25]. A coefficient of repeatability less than ±2 mm in 95% of the cases is considered acceptable. If this target is not achieved, further examiner assessment and training will be carried out before a new reproducibility exercise is performed.

#### Clinical photographs

Clinical photographs and videos of completed procedures will be taken in some of the study visits for better documentation of cases and will be anonymised and stored in the study database.

#### Radiographic analyses

Standardised radiographs of selected study sites will be taken at baseline and at the 9 and 15 months follow-up visits using the parallel technique with a customised holder and an occlusal platform, which will allow a cold-cure acrylic resin occlusal registration to be made (bite index), facilitating relocation of the holder and preserving the projection geometry in subsequent radiographs. Aluminium step wedges will be used as a densitometric reference in an attempt to minimise errors due to variation in exposure time and/or film processing which may result in false positive analysis [26]. The linear radiographic measurement analysis will be carried out by a single calibrated examiner using semi-automated radiographic software with specific landmarks, as described by Nibali et al. [27]. In brief, horizontal and vertical bone loss of the intrabony defects will be measured after identifying the following landmarks in periapical radiographs: CEJ on the tooth with the intrabony defect, most coronal part of the alveolar bone and most apical part of the alveolar bone crest, where the periodontal ligament space was judged to retain its normal width. The radiographs will be analysed by the same trained and calibrated examiner in a masked, random order with the use of a computer software measurement tool (Emago®, Oral Diagnostic Systems, Amsterdam, the Netherlands).

#### Test procedure (MINST)

Based on our previous study [17], a modified MINST protocol for this study consists of the following:Local anaesthesia by infiltration without adrenaline in the study site (not intrasulcular anaesthesia)Thorough debridement of the root surface up to the bottom of the periodontal pocket under local anaesthesiaAttempt to minimise the trauma to the soft tissues and especially to the papilla, using a subpapillary access for debridement (trying not to touch the most coronal part of the interdental papilla)Use of exclusively piezo-electric devices with specific thin and delicate tipsDeliberately avoid ‘smoothing’ the root surface or performing gingival curettageUse of 3–4× magnification loupesAttempt to stimulate the formation of a stable blood clot, by natural filling of the intrabony defect with blood following debridement (no use of any subgingival rinses).

This modified protocol differs slightly from the published protocol [17] in the use of a subpapillary access; exclusively piezo-electric devices (no curettes); the specific use of anaesthesia without adrenaline and no intrasulcular anaesthesia; and the first subgingival probing at 6 months post-treatment (rather than at 3 months). These slight refinements from the earlier studies [17] aim to further reduce tissue trauma and to stimulate a stable blood clot for optimal healing. This modified MINST protocol will be applied to the intrabony sites and all other affected sites in test patients. The same treatment protocol is currently being tested in a separate single-arm prospective multicentre study (ClinicalTrials.gov reference NCT03741374).

#### Control procedure (M-MIST)

This will be performed as described in the literature [14, 28]:Scaling and root planing using conventional ultrasonic tips and curettes under local anaesthesiaPeriodontal re-evaluation and charting 3 months laterIn case of residual PPD > 5 mm, surgical access with the following protocol:Ideally, the experimental sites will be accessed with the M-MIST technique (elevation of buccal flap only with simplified or modified papilla preservation incisions, no papilla elevation) and carefully debrided.When a defect wraps around the lingual aspect of a tooth and M-MIST is not applicable, elevation of the interdental soft tissues becomes necessary and MIST becomes the preferred approach. This consists of elevation of small buccal and lingual flaps (with modified papilla preservation incision in case of interproximal space width of at least 2 mm or otherwise simplified papilla preservation [29].When the position of the residual buccal/lingual bony wall(s) is very deep and difficult or impossible to reach with the above-described minimal incision of the defect-associated interdental space, the flap(s) will be further extended mesially or distally involving one extra interdental space to obtain a larger flap reflection [29].

Should the FMPS not reach the threshold below 25% before surgery, additional oral hygiene (OH) instructions will be given before proceeding with the surgical intervention. If after three additional OH sessions, the FMPS is still not below 25%, the patient will be exited from the study as not considered suitable for surgery [30]. Measurements will be taken during surgery to characterise the defect anatomy (number of walls, depth and width). No regenerative material/devices will be applied. Flaps will be sutured with modified internal mattress sutures (and single interrupted sutures if necessary).

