The sample size calculation was based on the assumption that the proposed modified MINST protocol is an acceptable alternative to the M-MIST protocol (non-inferiority), with the advantage of reduced costs and morbidity. A non-inferiority margin of 1 mm is considered to be the largest difference that is acceptable between MINST and M-MIST (a lower threshold than the expected difference in bone gain between regenerative surgeries and open flap debridement in intrabony defects) [12] for MINST to be adopted in clinical practices because of the associated advantages of MINST. Single-flap approaches such as M-MIST have previously been reported to lead to radiographic bone gains from 1.8 ± 1.2 mm [37] to 2 mm [38] to 3.5 ± 1.0 mm [14] in small trials. MINST has been reported to lead to 2.4 ± 2.1 mm radiographic bone gain in a retrospective study [17]. Therefore, we assume that the two protocols lead to the same bone gain for the sample size calculation. Accounting for a 10% drop-out rate and using a pooled standard deviation of 1.27, recruiting *n* = 66 participants will be sufficient to confer 90% power to reject the inferiority null hypothesis. Should the true mean bone gain difference between MINST and M-MIST be 0.19 mm in favour of M-MINST, the study would retain a statistical power of 80%. The primary outcome analysis will compare the intrabony defect depth between treatment groups at 15 months using a general linear analysis of covariance (ANCOVA) model with treatment as a factor and the corresponding baseline value as a covariate and adjusting for pre-specified prognostic baseline factors (age, FMPS, BMI, defect angle, tooth mobility). For the primary efficacy endpoint, non-inferiority of M-MIST to MINST could be claimed if the lower limit of the 95% confidence interval (for the difference in mean change of radiographic intrabony defect depth change) is greater than − 1.0 mm. The primary outcome analysis will be the per-protocol analysis; the intention-to-treat analysis will be considered as the sensitivity analysis. For other non-inferiority endpoints the per-protocol analysis will also be considered the main analysis. The superiority endpoint will be analysed on an intention-to-treat basis. Subject-based and site-based analyses will be conducted. The PROM analysis will be based on linear or logistic regression (for continuous/categorical variables) comparing PROM scores or categories of scores at follow-up (3, 9 and 15 months post-intervention) between the two groups, accounting for the respective scores at baseline. We will also look at the minimally important difference for PROMs where applicable, such as in the case of the OIDP, and whether any difference between the two groups is clinically meaningful.

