#### Randomisation and allocation concealment

Following the baseline visit, all participants enrolled in the study will be randomly assigned to one of the two treatment groups and whether or not to be included into the GTI substudy; that is, individual-level randomisation to MINST, M-MIST, MINST + GTI or M-MIST + GTI will be performed using a 2:2:1:1 allocation ratio. Random permuted block randomisation with block sizes 6 and 12 will be employed. The centralised online randomisation service ‘Sealed Envelope’ with web front-end will be used ensuring allocation concealment. No minimisation or stratification is planned.

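### A plaque-based exit that applies only to control patients after randomisation leaves the intention-to-treat analysis without observed outcomes for a selected part of one arm

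*Protocol article*

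**What the plan says.** Randomisation comes early. Under Randomisation and allocation concealment: "Following the baseline visit, all participants enrolled in the study will be randomly assigned to one of the two treatment groups".

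The Control procedure (M-MIST) section starts with conventional scaling and root planing, re-evaluates at 3 months, and sends patients with residual PPD above 5 mm to surgery. If their full-mouth plaque score (FMPS) is not below 25%, they receive extra oral hygiene instruction. Then: "If after three additional OH sessions, the FMPS is still not below 25%, the patient will be exited from the study". The reason given is that the patient is "as not considered suitable for surgery".

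The Test procedure (MINST) section has no plaque threshold and no exit. It says "This modified MINST protocol will be applied to the intrabony sites and all other affected sites in test patients" and describes the technique. Table 1 lists "Plaque assessment" at the 3-month visit without restricting it to one arm. The only other exit rule, in the section on risks, follows an adverse event and applies to both arms.

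The Statistical analysis plan section includes FMPS among the "pre-specified prognostic baseline factors (age, FMPS, BMI, defect angle, tooth mobility" covariates. On analysis sets it says: "The primary outcome analysis will be the per-protocol analysis; the intention-to-treat analysis will be considered as the sensitivity analysis".

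**The concern.** The exit takes effect at or after the 3-month visit, so it is a post-randomisation event. Its stated reason, unsuitability for surgery, can arise only in the arm that has surgery. A MINST patient with the same plaque score is recorded and, as far as the article states, continues.

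The wording removes the patient from the study, not only from surgery. The primary outcome is radiographic change at 15 months, and nothing in the article provides that radiograph for an exited patient. If those who leave would have healed less well than the controls who remain, the observed control mean is too high and the comparison is tilted against MINST. The intention-to-treat analysis is meant to be the check on the per-protocol result, yet it would lack observed outcomes for the same controls.

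**Working it through.** **1. The texts side by side.**

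| Feature | Control (M-MIST) | Test (MINST) |
|---|---|---|
| Randomised | after baseline visit | after baseline visit |
| Plaque assessed at 3 months (Table 1) | yes | yes |
| FMPS threshold of 25% | yes, if due for surgery | none stated |
| Exit from study on plaque | yes, after three further hygiene sessions | none stated |
| 15-month radiograph after such an exit | not provided for | not applicable |

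The ANCOVA adjusts for baseline FMPS. The exit depends on FMPS at 3 months and later, among patients who also have residual deep pockets. Baseline adjustment removes only the part of that selection that baseline FMPS predicts.

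**2. The plan's own sample size.** Inputs from the Statistical analysis plan section: margin 1 mm, SD 1.27, true difference 0, power 90%, drop-out 10%. With a noncentral t calculation at one-sided 5%, 29 per arm are needed; 29/0.9 rounds up to 33 per arm, or 66 in total, as stated. At one-sided 2.5%, which a two-sided 95% interval implies, 35 per arm are needed, giving 78. The choice of level is a separate matter, so both are shown below.

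**3. Effect of the exits.** Let q be the share of controls exited and D the amount by which they would have healed less than the remaining controls. The documents give neither; both are assumptions.

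- Shift in the control mean = q × D.
- Evaluable MINST patients = 33 × 0.9 = 29.7; evaluable controls = 29.7 × (1 − q). This treats exits as additional to the 10% drop-out.
- SE = 1.27 × √(1/n₁ + 1/n₂); noncentrality = (1 − qD)/SE; degrees of freedom n₁ + n₂ − 2.

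No exits: SE = 1.27 × √(2/29.7) = 0.3296; noncentrality 1/0.3296 = 3.034; power 0.847 at one-sided 2.5% and 0.912 at 5%.

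q = 10%, D = 1.0 mm: shift 0.10 mm; controls 26.73; SE = 1.27 × √(1/29.7 + 1/26.73) = 0.3386; noncentrality 0.90/0.3386 = 2.658; power 0.742 and 0.836.

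| Exits (D = 1.0 mm) | Shift | Power, one-sided 2.5% | Power, one-sided 5% |
|---|---|---|---|
| none | 0 | 0.85 | 0.91 |
| 3% (1 of 33) | 0.03 mm | 0.82 | 0.89 |
| 10% | 0.10 mm | 0.74 | 0.84 |
| 20% | 0.20 mm | 0.61 | 0.73 |

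For D from 0.5 to 1.5 mm at one-sided 2.5%, power is 0.79 to 0.69 with 10% exits and 0.71 to 0.50 with 20%.

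A yardstick from the plan: it states that a true difference of 0.19 mm lowers power from 90% to 80%. Only the 20% row has a shift of that size.

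**The case against.** **Direction.** A reader might infer that the rule endangers a non-inferiority conclusion. The documents do not support that. Taking poor healers out of the control arm makes M-MIST look better, so the expected bias is conservative for MINST. What remains is a tilted estimate and a greater chance of a false failure.

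**Size.** The rule has three gates: residual PPD above 5 mm at 3 months, FMPS not below 25%, and no success after three further sessions. Few patients may reach the end, and with one exit the effect is small. That FMPS predicts healing rests on its listing as a prognostic covariate, with no effect size. This stands in full; the figures above are illustrations.

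**Analysis sets.** A reader might infer that neither analysis can use these patients, or that the intention-to-treat set stops being one. That goes too far. Set definitions and missing-data handling may sit in an analysis plan that is not shown. But such a plan could only impute these outcomes; it could not recover radiographs that were never taken.

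**Hygiene sessions.** The extra sessions might be read as a second bias. They can equally be part of the surgical strategy under comparison, and a condensed article's silence about hygiene support in the MINST arm does not show that there was none.

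**Per-protocol set.** A control due for surgery who does not have it would ordinarily fall outside the primary per-protocol set even if followed to 15 months. This is correct and limits what any change in follow-up can achieve.

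**Conclusion.** The point holds in a limited form and should be fixed. The article sets out a one-sided, post-randomisation exit that depends on a factor it treats as prognostic, and makes no provision for the 15-month outcome of those who leave. This weakens the intention-to-treat analysis as a check on the per-protocol result. It can bias the estimate against MINST and lower power; it is not expected to inflate a non-inferiority claim.

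The size is unknown. With a 1.0 mm deficit the loss of power at one-sided 2.5% runs from about 3 points (3% exits) to about 24 points (20%). This rests on the assumed exit share and deficit, on the plan's SD and zero true difference, and on exits adding to the 10% drop-out. If the allowance was meant to cover them, the loss of sample size is smaller but the shift is unchanged. That MINST patients stay in is read from the absence of any stated rule.

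**What to change.** Leave the decision on suitability for surgery, and the care that follows it, to the protocol team. Change only the consequence for follow-up: state that not proceeding to surgery is not the same as leaving the study. With their consent, these patients stay in the visits already scheduled, including the 9- and 15-month radiographs, and enter the intention-to-treat analysis as randomised.

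Report how many controls did not proceed to surgery on plaque grounds, with the reason. Read the per-protocol result next to this more complete intention-to-treat result, since the former would still ordinarily leave them out.

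Do not try to restore balance with a 3-month FMPS cut-off for the per-protocol set in both arms. It would not match the control gate, which uses FMPS after further sessions in patients with residual pockets. It would also drop controls who later fall below 25% and have surgery as planned, which is a new post-randomisation selection.

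The cost is a short amendment and some further follow-up visits and radiographs for what may be a handful of patients. It needs to come before patients are exited, because a missed radiograph cannot be recovered.
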